## Abstract

**Background:**

Pes planus is one of the most common foot deformities. Although there are many studies on the effectiveness of various exercise methods in pes planus rehabilitation, the number of studies on video-based game exercise therapy applications is very limited.

**Objective:**

This study aims to evaluate the effectiveness of 2 video-based game exercise therapies and structured exercise practices in pes planus rehabilitation.

**Methods:**

This study is a 3-arm, parallel-group, single-blinded randomized controlled trial. The study will include 69 patients with flexible pes planus aged between 18 and 25 years who attend the orthopedics and traumatology clinic and meet the inclusion criteria. The primary outcomes are measures of navicular drop and pedobarographic analysis before and after the intervention, and the secondary outcomes include balance, femoral anteversion, and lower extremity muscle strength. Participants will be evaluated with a navicular drop test for medial longitudinal arch height, a pedobarographic analysis system for plantar pressure analysis, a Craig test for femoral anteversion, the Becure Balance System for balance measurement, and a myometer device for lower extremity muscle strength measurement. Participants will be randomly assigned to a structured exercise group, an exergame group, or a serious game group according to their order of arrival. The structured exercise group will use a short foot exercise, a towel-picking exercise, and various walking and balance exercises. Patients in the serious play group will play the lower extremity games in the Becure Balance System. Patients in the exergame group will play balance games on the Nintendo Wii game console. All participants will participate in 18 exercise sessions (3 days a week for 6 weeks). After the treatment, the initial measurements will be repeated.

**Results:**

The study started in January 2023. It is expected to be completed in June 2024.

**Conclusions:**

This study will be the first randomized controlled study to evaluate the effectiveness of 2 different video-based game exercise therapy applications in pes planus rehabilitation. Through this study, the use of video-based game exercise therapy in pes planus rehabilitation, together with the developing technology, will be a guide. In addition, a new exercise protocol, including serious game exercises, will be added to the literature. In the future, it is expected that our study on the development of different game systems, especially for the ankle, will provide pioneering feedback.

**Trial Registration:**

ClinicalTrials.gov NCT05679219; https://clinicaltrials.gov/study/NCT05679219

**International Registered Report Identifier (IRRID):**

DERR1-10.2196/51772

## Introduction

Pes planus, one of the most common foot deformities in all age groups, is defined as the condition where the medial longitudinal arch (MLA) chronically loses its height [1]. The most significant problem with pes planus is excessive pronation during load-bearing activities. Increased pronation of the subtalar joint causes the tibia to remain in internal rotation (IR) longer than usual during walking. For this reason, valgus stress occurs in the knees and IR increases in the hips. Anterior tilt is seen in the pelvis, increasing lumbar lordosis [2-5]. Complaints of pain, fatigue, and weakness while walking and standing may also accompany the symptoms [6]. Previous studies show that pes planus affects the mobility of the MLA, increases stress on the foot, and causes impaired load distribution; it also causes posterior tibial tendon failure, patellofemoral pain syndrome, and compensatory hip internal rotation. These have been reported to negatively affect performance and balance [7-10].

Pes planus deformity can be seen together with pain, instability, and various functional limitations, or it can be mild. However, the biomechanical changes caused by the deformity may increase over the years and cause clinical symptoms and functional problems. Therefore, even if pes planus is asymptomatic in young adults, it should be treated considering the problems it may cause in the future. Treatment can be surgical or conservative, depending on symptoms and clinical assessment. Conservative treatment options include activity modifications, analgesic drugs, physiotherapy, and orthotics. The physiotherapy program includes intrinsic foot exercises, stretching, strengthening and balance exercises for the ankle and lower extremity muscles, and video-based game exercise (VBGE) programs. The literature on rehabilitation of pes planus includes studies on the effects of exercise practices on the MLA, foot biomechanics, and balance [11-18].

Pes planus is a pathology that requires long-term rehabilitation. Considering the secondary pathologies that the deformity may cause, rehabilitation protocols that have high participation from an early period are needed. This makes VBGE treatments, which are becoming increasingly widespread in rehabilitation with the development of technology, come to mind. The literature describes VBGE treatments as exergames, serious games, and rehabilitative games.

Exergames are the therapeutic application of commercially developed video games in an exercise form. Exergame applications use game systems such as the Wii (Nintendo Inc), Xbox Kinect (Microsoft Corp), and PlayStation Move (Sony Inc), which were produced for entertainment purposes and are frequently used in rehabilitation. [19,20]. It has been reported that lower extremity games for the Xbox applied for 12 sessions in patients with flexible pes planus improved balance and navicular drop [12]. Serious games are games developed for rehabilitation rather than entertainment purposes. These games are developed specifically for a certain disease group or disease symptoms. Thus, they aim to provide rehabilitation by increasing active participation in therapy with higher motivation. One of the systems developed for this purpose is the Becure system, formerly known as Fizyosoft. The Becure system has software that can integrate with the Wii Balance Board. Studies in the literature show that Becure games lead to positive results in different disease groups [21-25]. However, there has been no study conducted with serious games for pes planus.

Today, the rapid development of technology and patients’ search for new treatments have made it necessary to add these technologies to the rehabilitation process. There are many studies in the literature on VBGE therapy in different patient groups. However, there is a lack of literature regarding VBGE therapy in individuals with flexible pes planus. There is only one study, which used the Xbox Kinect [12]. Thus, we aim to compare the effects of different exercise protocols on functional parameters in pes planus rehabilitation. Also, our study will contribute to the literature by being the first study to compare Wii-based exergame protocols and Wii-based serious game exercise protocols.

## Methods

### Participants

The number of cases to be included in the study was determined by G*Power (version 3.0.10; Universitat Düsseldorf). Navicular drop test results from the study by Yıldırım Şahan et al [12] were taken as a reference. For α=.05 (error), 1–β=95% (power), and *f*=0.49 (effect size), we determined that it would be necessary to include a total of 69 people, with 23 in each group.

Participants will be recruited among individuals aged 18 to 25 years who attend the Medipol Mega University Hospital Orthopedics and Traumatology Department. The study will include 69 individuals who volunteer to participate and meet the inclusion criteria. The inclusion criteria were a navicular drop of more than 10 mm, flexible pes planus, and no previous use of insoles or exercise therapy. At the same time, since excess weight can affect pes planus, only individuals with a BMI within the range of 18 to 24.9 kg/m^2^ will be included. Individuals with orthopedic or neurological problem affecting the lower extremities and balance, a history of surgery or trauma in the last 6 months, diabetes, pregnancy, or visual or auditory problems will also be excluded from the study.

### Ethical Considerations

The study was approved by the Istanbul Medipol University Non-Interventional Clinical Research Ethics Committee (E-10840098-772.02-7170; November 28, 2022). The Declaration of Helsinki will guide the study. After eligibility is confirmed, written and verbal information about the study will be provided to all participants. Then, participants will sign a written informed consent form stating that they agree to participate in the research. The informed consent form also states that participation in the study is free and voluntary. No additional fees will be charged to the participants, and no payment will be made. The personal data and identity information of the participants will be kept confidential. Participants have the right to withdraw from the study at any time. The data will be used purely to contribute to science without any profit motive. At the same time, the data can be statistically analyzed without secondary approval when necessary. The trial intervention is similar to other clinical practices, so we consider that risks from the trial are minimal.

### Study Design

This study has been registered with ClinicalTrials.gov (NCT05679219). It is a 3-arm, parallel-group, single-blinded randomized controlled trial. The study will be carried out in Istanbul Medipol University Physiotherapy Laboratory. A permit has been obtained from the institution. The demographic characteristics of the participants (eg, age, height, weight, diseases) will be recorded. Participants will be divided into 3 groups using a simple randomization method according to the order of arrival (1:1:1) with a web-based randomizer [26]. Participants do not know which exercise group they will be included in, nor will they know the differences between the exercises. The participants and the therapist who made the assessments were blinded. The flow chart of the study is shown in Figure 1.

**Figure 1 figure1:**
[figure not shown]
Study flow diagram.

### Outcome Measures

The primary outcome measures are navicular drop and the results of a pedobarographic analysis, and the secondary outcomes include balance, femoral anteversion, and lower extremity muscle strength. Participants will be evaluated before and after treatment. Measurements will be taken by an experienced therapist, who will not be the same therapist as the one who performs the exercises. The therapist performing the measurements will create the random allocation order, enroll the participants, and assign the participants to the interventions.

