### Pedobarographic Analysis

The pedobarographic analysis will be done in 2 steps, statically and dynamically, with the Sensor Medica Maxi brand device (Sensormedica). Static analysis data will be recorded while standing upright. Dynamic analysis data will be recorded while walking on the platform 6 times. Data such as ankle valgus angle, medial arch, lateral arch, medial heel, lateral heel surface area (cm²), and load (%) will be recorded. Plantar pressure analyses will be determined through FreeStep (version 1.6.009; Sensormedica), which is compatible with the device (Figures 2 and 3) [27].

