### Statistics

Data will be statically analyzed using SPSS (version 25.0; IBM Corp). Normality tests (visual and analytical) will be applied. Descriptive statistics will be expressed as arithmetic means with SDs. After obtaining the results of the normality evaluation, analyses will be carried out with tests suitable for the distribution of the groups. Statistical analyses will be interpreted according to the significance level of *P*<.05.

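### The second primary outcome is an open-ended pedobarographic battery with no named variable and no stated rule for combining it with navicular drop, on which alone the sample size rests

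*Protocol article*

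**What the plan says.** The abstract and the Outcome Measures section give two items primary status: "The primary outcome measures are navicular drop and the results of a pedobarographic analysis". Balance, femoral anteversion and muscle strength are secondary.

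The content of the second primary is described only in the Pedobarographic Analysis section: "Data such as ankle valgus angle, medial arch, lateral arch, medial heel, lateral heel surface area (cm²), and load (%) will be recorded". The same section adds: "The pedobarographic analysis will be done in 2 steps, statically and dynamically". It picks out no variable, measurement condition or summary value as the primary one.

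The Statistics section gives one criterion for everything: "Statistical analyses will be interpreted according to the significance level of *P*<.05". It mentions no ordering of the primaries, no division of alpha and no rule for combining them.

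The sample size in the Participants section starts from one outcome, "Navicular drop test results from the study" of video-game exercise in flexible pes planus that the article cites. With alpha .05, power 95% and f=0.49 it concludes: "we determined that it would be necessary to include a total of 69 people, with 23 in each group".

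**The concern.** The output of a measuring system is not an endpoint. As worded, any of several plantar-pressure variables, standing or walking, could be presented as a primary result, and the text does not tie the authors to one of them in advance. Nor does it say what follows if navicular drop shows no difference and one pressure variable does, or the reverse.

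This matters because the Discussion says the trial will establish whether game-based exercise is superior to structured exercise. If one nominally significant variable out of the battery is enough for that claim, the error rate of the claim is that of the whole family of tests and not the 5% of each test.

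**Working it through.** **1. The plan's own figure.** The article does not name the test behind the sample size. The omnibus one-way ANOVA F test for three groups reproduces it. Power is the probability that a noncentral F with 2 and N−3 degrees of freedom and λ = f²N exceeds the central critical value.

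- N=69: λ = 0.49² × 69 = 0.2401 × 69 = 16.57, df 2 and 66, alpha .05: power 95.5%.
- N=66: power 94.5%, below target.

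So 69 is the smallest total with equal groups that reaches 95%. It corresponds to one test of navicular drop at the full .05, with no allowance for a second primary.

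**2. How many primary tests?** The article gives no number. These counts are assumptions, with one omnibus test per variable and navicular drop as one test:

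- 7 = 1 + 6 (each listed item counted once)
- 10 = 1 + 9 (one angle, plus area and load for each of four regions: 1 + 4×2 = 9)
- 13 = 1 + 6×2 (six items, static and dynamic)
- 19 = 1 + 9×2 (nine variables, static and dynamic)

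**3. Chance of at least one false positive.** Assume no true difference on any variable, each tested at .05, with any one significant result counted as a primary finding. For m independent tests the chance is 1 − 0.95^m. For correlated tests it was simulated with three groups of 23, equally correlated normal outcomes and one F test each (10,000 to 20,000 simulated trials per setting). The correlations are assumptions; the documents give none.

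| Tests m | Independent | Correlation 0.5 | Correlation 0.9 |
|---|---|---|---|
| 7 | 1 − 0.95^7 = 30.2% | 23.8% | 12.1% |
| 10 | 1 − 0.95^10 = 40.1% | 29.0% | 13.1% |
| 13 | 1 − 0.95^13 = 48.7% | 34.4% | 15.1% |
| 19 | 1 − 0.95^19 = 62.3% | 42.2% | 16.3% |

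For reference, two tests give 1 − 0.95² = 9.75% if independent and about 7% at correlation 0.9. The rate passes 50% only from 14 independent tests (1 − 0.95^14 = 51.2%), and later if they are correlated. Unadjusted pairwise contrasts among the three arms, or analysing each foot separately, would raise the figures.

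**4. Cost of the alternatives at N=69 and f=0.49.**

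- Navicular drop alone at .05: power 95.5%.
- Two primaries, navicular drop tested at .025: power 91.8%; 95% would need N=78. Holm tests the smaller p-value at .025 and, if that succeeds, the other at .05, so 91.8% is a lower bound for navicular drop under Holm.

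**The case against.** The strongest reply is that this is a condensed article. A multiplicity procedure is commonly left to an analysis plan or full protocol, neither of which is shown, and the registry entry may name specific variables. That stands as far as it goes: the article can be said to state no error control, not that none exists. It does not excuse the undefined outcome. Naming the primary variable is the protocol's own job, and the section devoted to this measurement offers examples where the variable should be named.

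Second, the article says these data will be recorded. It does not say that each variable is a separate primary test, or that one significant result suffices. It joins the two primaries with a plain conjunction and never defines success. This also stands: the variable counts and the any-one-wins rule are readings of the text, and the family-wise figures hold only under them. Not every variable need be taken in both conditions, so 19 is a high count for one value per participant.

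Third, area and load on adjoining regions of the same foot are unlikely to be independent, so the independent column is best treated as an upper bound for each count.

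Finally, sizing a trial on one of two primary outcomes is not in itself an error, and a single test of navicular drop keeps its 5% level whatever is done with plantar pressure.

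**Conclusion.** The point holds as a badly fixed primary outcome. The second primary is a battery with no named variable, the only stated criterion is P<.05, no rule links the two primaries, and the sample size makes no allowance for more than one primary test.

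If any one variable can support a primary claim, the chance of at least one false-positive primary is above 5% on every setting examined: from about 12% (7 tests, correlation 0.9) to about 62% (19 independent tests), with 24–42% at correlation 0.5. These figures rest on assumed counts, assumed equal correlations, one omnibus test per variable and no true differences.

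A reader might infer that a false-positive primary result is more likely than not. The documents do not support that, because it takes at least 14 independent tests and they give neither the number of variables nor their correlation. A reader might also infer that the alpha of .05 in the sample size calculation is invalid. It is not: that alpha belongs to the navicular drop test, which is unaffected.

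**What to change.** Settle this before any data are analysed. The Results section says analysis waits until all scheduled participants have completed treatment, so the plan itself leaves room for it.

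- **Preferred:** make navicular drop the sole primary outcome, with one pre-named value per participant (for example the mean of both feet, or one pre-named foot). Move all pedobarographic variables to secondary or exploratory. N=69 and 95.5% power stand unchanged.
- **If plantar pressure must stay primary:** name one variable and one condition (for example the dynamic load of one region) and test it and navicular drop with Holm at a total of 5%. On the plan's own f=0.49, power for navicular drop is then at least 91.8%. Power for the pressure variable cannot be worked out, because the article gives no effect size for it.

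Make the registry entry consistent if it differs. The change is one of wording and needs no new visits, measurements or participants. The cost is that the other pressure findings lose primary status and, under the second option, there may be a modest loss of power for navicular drop.

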In recent years, VBGE therapy applications have been used frequently in orthopedic rehabilitation, in accord with patients’ search for new treatments and the development of technology. There are studies showing that video-based exercise applications lead to positive results in different patient groups [19-25]. However, there are insufficient studies on these applications for pes planus rehabilitation. There is only one study in cases with pes planus. Yıldırım Şahan et al [12] divided 40 patients with flexible pes planus into 2 groups and compared the effects of Microsoft Xbox Kinect lower extremity games and short foot exercises performed 3 days a week for 4 weeks. They found a significant improvement in both groups’ navicular drop and balance data after treatment. They reported that VBGE was an effective exercise method in patients with pes planus. However, the study’s limitations were a limited number of participants, a short duration of treatment (12 sessions), and a lack of objective evaluation methods.

Compared to the study by Yıldırım Şahan et al [12], we used a relatively longer session duration (18 sessions), included a large number of cases, and used only objective evaluation methods, thereby increasing the importance of our study. However, it is known that games for the Nintendo Wii game console (exergames) and the Becure Balance system (serious games) are designed to improve the overall body balance. Therefore, it is unclear to what extent exercises for the intrinsic and extrinsic muscles of the feet are included in the content of both video-based games. They are likely to have similar potential effects. This situation can be considered as a limitation of our study. But at the same time, thanks to our study, the effectiveness of these games in the rehabilitation of pes planus will be determined, and the ground will be prepared for the development of specific games for the treatment of foot and ankle pathologies in the future.

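### The plan calls the outcome assessor blinded, yet has that same therapist create the allocation order, enrol and assign, so assessor blinding is not delivered as written and allocation concealment is unprotected

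*Protocol article*

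**What the plan says.** All of this comes from the Methods of the protocol article.

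- **Study Design, label:** "It is a 3-arm, parallel-group, single-blinded randomized controlled trial".
- **Study Design, allocation:** participants are divided "using a simple randomization method according to the order of arrival (1:1:1) with a web-based randomizer".
- **Study Design, blinding:** "The participants and the therapist who made the assessments were blinded". For participants this is explained as follows: "Participants do not know which exercise group they will be included in, nor will they know the differences between the exercises".
- **Outcome Measures, timing:** "Participants will be evaluated before and after treatment".
- **Outcome Measures, roles:** "Measurements will be taken by an experienced therapist, who will not be the same therapist as the one who performs the exercises". Then: "The therapist performing the measurements will create the random allocation order, enroll the participants, and assign the participants to the interventions".

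Navicular drop and pedobarography are the primary outcomes. Balance, femoral anteversion and lower extremity muscle strength are secondary. A navicular drop above 10 mm is also an entry criterion, and navicular drop results from an earlier study are the basis of the sample size (Participants).

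**The concern.** One therapist holds four tasks: making the allocation order, enrolling, assigning and measuring. The only separation the article gives is between the measuring and the treating therapist. That keeps the person delivering the exercises away from the outcomes, but it does not keep the arm from the person who measures them.

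Two biases are at stake. The first is detection bias: an assessor who knows the arm can, without intending to, read or prompt differently by arm after treatment. The second is selection bias: if the person who decides on eligibility can foresee the next arm, the decision or its timing may depend on that arm. Both can act on navicular drop, which is at once entry criterion, primary outcome and sample-size basis. The Discussion counts it as a strength that the trial "used only objective evaluation methods", and a measurer who knows the arm weakens that claim for any outcome that depends on the examiner.

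**Working it through.** **1. Assessor blinding.** Set the two statements side by side.

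- Study Design: the assessing therapist is blinded.
- Outcome Measures: the measuring therapist assigns participants to interventions, and measurement takes place before and after treatment.

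Assigning a person to an arm entails knowing the arm. The post-treatment measurement comes after assignment and is made by the same therapist. The second statement therefore contradicts the first, and nothing else in the article reconciles them.

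**2. Concealment.** The therapist creates the order and enrols. Allocation follows order of arrival. A web-based randomizer is named, but the article does not say when each draw is made or who can see the result in advance. No sealed, central or independently held list is described. Concealment is therefore unprotected as described, though not shown to be impossible.

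**3. Which outcomes are exposed.**

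| Outcome | How obtained, per the article | Exposure to an assessor who knows the arm |
|---|---|---|
| Navicular drop (primary) | Technique not spelled out; taken to be an examiner's measurement | High, on that assumption |
| Craig test (secondary) | Goniometer reading | High |
| Muscle strength (secondary) | Myometer | High |
| Pedobarography (primary) | Platform and software | Lower; instruction and positioning still matter |
| Balance (secondary) | Reported by the Becure system | Lower, for the same reason |

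**4. The plan's own sample size.** Inputs from Participants: α = 0.05, power 95%, f = 0.49, three groups. For the one-way F test the noncentrality is λ = f² × N = 0.49² × 69 = 16.57, with 2 and 66 degrees of freedom. Power is 0.9546 at N = 69 and 0.9454 at N = 66, so 69 is the smallest balanced total and the stated figure is reproduced. Changing who allocates does not alter it.

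**5. Illustrative size of detection bias.** The documents give no bias figure. Assume no true effect and a systematic measuring shift of d SD, with 23 per arm and two-sided 5% tests.

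- *Two-arm t test:* noncentrality = d × √(23/2), with 44 degrees of freedom. For d = 0.25 this is 0.848 and the rejection rate is 0.132. For d = 0.50 it is 1.696 and the rate is 0.382.
- *Three-group F test:* λ = 23 × the sum of squared deviations of the arm shifts from their mean.

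| Shift d (assumed) | t test, two arms | F test, shifts 0, d/2, d | F test, one arm shifted by d |
|---|---|---|---|
| 0.25 SD | 0.132 | 0.105 | 0.125 |
| 0.50 SD | 0.382 | 0.297 | 0.384 |

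These rates show how sensitive the trial would be to such a shift. They do not show that a shift occurred.

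**The case against.** The strongest reply is that the contradiction may be one of wording. The blinding statement is in the past tense and the allocation statement in the future, and the Results section says that about 7 patients per group had already completed treatment. If the assessor was in fact kept unaware, correcting the sentence in Outcome Measures suffices. This stands: the article does not establish what was done. A reader might infer that everyone already assessed was measured unblinded, but the text does not support that as a fact.

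Second, a reader might infer that allocation concealment is impossible under this plan. That goes too far. A web draw made only after irrevocable enrolment would hide the next arm even with the same person operating the tool. The article does not describe such a draw, and its reference to creating an order suggests a list made beforehand, without proving it. Such a draw would not restore assessor blinding in any case, since the therapist would still make the assignment.

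Third, a reader might infer that any between-arm difference could be put down to the measurer. Pedobarography and balance are recorded by devices, so that is too broad.

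Fourth, the shifts of 0.25 and 0.50 SD come from no document, and the resulting rates depend on the test and on how the shift is spread over the arms. This stands, and the point does not rest on them.

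Fifth, the participant-blinding claim can be read as unawareness of how the arms differ, not of one's own activity. That is a fair reading. Participants plainly know whether they do towel curls or play a console, and a single-blind label sits awkwardly with two parties said to be blinded, but these are matters of labelling.

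That an article condenses a fuller protocol is no answer to the main point. It states both things, and no longer document can make them compatible without withdrawing one.

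**Conclusion.** The point holds as a contradiction in current text, and it must be resolved because it touches a primary outcome. As written, the plan does not deliver the assessor blinding it claims, and it leaves allocation concealment unprotected. The consequence is mainly a risk of detection bias in navicular drop, the Craig angle and muscle strength. For navicular drop this assumes an examiner-dependent technique, which the article does not spell out.

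The size of the bias is unknown. Under the assumed shifts, the nominal 5% error rate becomes 10.5% to 13.2% at 0.25 SD and 29.7% to 38.4% at 0.50 SD, depending on the test and the pattern across arms. The verdict rests on the two incompatible statements and not on these figures.

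**What to change.** 1. **Establish and disclose** who generated the order, enrolled, assigned and measured for participants already in the trial, and whether the next arm could be foreseen. Correct whichever statement is false. If the assessor was truly unaware of the arm, correcting the sentence in Outcome Measures is enough for blinding; describe also how the next arm was hidden.
2. **If the therapist does allocate as written**, then from the next participant on:
   - an existing team member who neither enrols nor measures generates and holds the list;
   - each assignment is released to the treating therapist only after eligibility and baseline measurements are recorded;
   - the measuring therapist has no access to the list;
   - participants are asked not to mention their exercises at the post-treatment assessment.

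   In that case report earlier participants as not assessor-blinded, state the date of the switch, and add a sensitivity analysis limited to those enrolled after it.
3. **Minor wording:** describe the trial as assessor-blinded only, once that is true, and replace the participant-blinding claim with a statement that participants are not told how the arms differ.

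The cost is a transfer of one task among existing staff and a short amendment. No extra visit or assessor is needed, and the sample size is unchanged. With about 7 of 23 per group treated at the time of writing, roughly 16 per group (23 − 7), or 48 of 69, had not yet completed treatment. The number not yet enrolled, who would gain the full protection, may be smaller and is not stated. The sensitivity analysis would be correspondingly imprecise.
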